##### Patient-Reported Outcomes Measurement Information System Measures

Several secondary outcomes are included from the Patient-Reported Outcomes Measurement Information System (PROMIS) [72-74], including alcohol negative consequences [75], Patient-Reported Outcomes Measurement Information System Preference (PROPr) score [76,77], and the PROMIS Meaning and Purpose measure [78]. The alcohol negative consequences measure includes 7 items scored from 1 (never) to 5 (almost always) that assess negative consequences from alcohol use (eg, I used poor judgment when I drank). Higher scores indicate more negative consequences. The PROPr combines scores from 7 PROMIS domains (cognitive function, depression, fatigue, pain interference, physical function, ability to participate in social roles and activities, and sleep disturbance) into a single health utility score. Higher scores indicate better health.

PROPr combines scores from 7 PROMIS domains (cognitive function, depression, fatigue, pain interference, physical function, ability to participate in social roles and activities, and sleep disturbance) into a single health utility score. Higher scores indicate better health. The Meaning and Purpose measure includes 8 items scored from 1 (not at all) to 5 (very much) that assess one’s sense that life has purpose and there are good reasons for living (eg, my life has meaning). Higher scores indicate greater purpose in life.

##### Penn Alcohol Craving Scale

The Penn Alcohol Craving Scale [79] is a 5-item measure of overall craving for alcohol. Responses range from 0 to 6, where 0 represents the absence of the craving and 6 represents the maximum intensity or frequency of the craving. Higher scores on the Penn Alcohol Craving Scale reflect more severe alcohol craving.

##### AUD Symptoms

The AUD Symptom Checklist [66] is a binary (yes or no), 11-item checklist of the symptoms of AUD experienced in the past 12 months (baseline assessment) and past 6 months (every 6 months at follow-up assessments). Higher scores indicate more symptoms of AUD.

##### Quality of Life

The World Health Organization Quality of Life–Brief Version (WHOQOL-BREF) [68] measure is a 26-item measure consisting of 4 domains: physical health (7 items), psychological health (6 items), social relationships (3 items), and environmental health (8 items); it also contains Quality of Life and general health items. Each item of the WHOQOL-BREF is scored on a 1 to 5 response scale, which is stipulated as a 5-point ordinal scale. The scores are then transformed linearly to a 0‐100 scale. Higher scores on the WHOQOL-BREF reflect a greater quality of life.

##### Self-Efficacy

The Harm Reduction Self-Efficacy Scale (HRSES) [80] is a 12-item measure that asks participants to indicate on a 0% to 100% scale regarding how confident they are that they would be able to resist drinking beyond their limit in a given situation. Higher scores on the HRSES reflect greater confidence to resist drinking beyond one’s limit.

##### Addiction Cycle Domains

The Addictions Neuroclinical Assessment has been used to represent domains of the addiction cycle and is assessed using a 12-item scale with 4 items for each domain [81]. The negative emotionality domain of the addiction cycle is characterized by temptation to drink in situations when the person is experiencing negative emotions. The Negative Emotionality Scale consists of 4 items scored on a scale from 1 (not at all tempted) to 5 (extremely tempted) to drink when experiencing negative emotions. Higher scores indicate a greater tendency to be tempted to drink in situations characterized by negative emotions. The incentive salience domain of the addiction cycle is characterized by temptation to drink in situations when the person is experiencing rewarding or social pressure to drink. The Incentive Salience Scale consists of 4 items scored on a scale from 1 (not at all tempted) to 5 (extremely tempted) to drink when experiencing rewarding, craving, or social situations. Higher scores indicate a greater tendency to be tempted to drink in situations characterized by reward, craving, and social pressure. The executive function domain of the addiction cycle is characterized by loss of control over drinking. The Executive Scale consists of 1 binary (yes or no) item (“After taking one or two drinks, can you usually stop?") and 4 items scored on a scale from 1 (indicating more control over drinking) to 5 (indicating loss of control over drinking). Higher scores indicate more impaired executive function and greater loss of control over drinking.

##### Purpose in Life

The Purpose in Life test [82,83] is a 20-item measure of experiencing meaning and purpose in one’s life, with each item assessed on a 1 (lack of meaning) to 7 (full of meaning) Likert-type scale. Higher scores indicate more meaning and purpose in life.

### Participant Timeline

From randomization, client participants are enrolled in the study for a total duration of 36 months. In total, there are 7 assessment sessions (enrollment, 6-, 12-, 18-, 24-, 30-, and 36-month follow-ups). The enrollment session lasts approximately 120 minutes (to allow for consent and interviewing), while the other assessment sessions last a maximum of 60 minutes. provides an overview of the schedule of assessment events for an individual study participant (Table 2).

**Table 2. T2:** Summary of study activities timeline.

Activity	Participant timeline
Phone or online screening	—^a^
Start of study participation: consent, randomization, and initial assessment (self-report measures, interview, and dried blood spot)	Month 0
Orientation session for randomized condition	Month 0
Attend MBRP^b^ groups or online mutual support groups	Month 0-36
6-month assessment	Month 6
12-month assessment	Month 12
18-month assessment	Month 18
24-month assessment	Month 24
30-month assessment	Month 30
End of study participation: 36-month assessment (self-report measures, interview, and dried blood spot card)	Month 36

a Not applicable.

b MBRP: mindfulness-based relapse prevention.

### Sample Size Considerations

Based on prior experience modeling outcomes over time and examining differences between MBRP and comparison groups, we are interested in powering the study to detect a small effect size difference between MBRP and referral to online mutual support in supporting recovery (primary outcome). We estimate power based on our prior efficacy trial [44] in which the difference at 12 months posttreatment on cessation of heavy drinking between MBRP and treatment as usual was a Cohen h=0.36. With a 2-tailed α of .05 and 430 participants (215 per group), we anticipate power greater than .90 to detect a similar effect size. To further ascertain power for the proposed set of analyses, Monte Carlo simulation studies were conducted to estimate power for testing the secondary outcomes given the proposed modeling approaches and likely parameter estimates. Power is greater than .90 for examining the effects of MBRP versus referral to mutual support on secondary outcomes over time. Given the use of modern missing data handling techniques [84,85] and an intent-to-treat design, we do not need to adjust sample size for potential attrition in the trial, although we aim to have 80% retention across the trial.

### Recruitment

Participants are recruited from web-based advertisements, posting of recruitment flyers throughout communities in targeted locations (including at treatment agencies and oft-visited locations near treatment agencies), online and social media recruitment sites, and links for recruitment on the homepage of study investigators. Recruitment materials include a QR code that is linked to a digital version (web page) of the participant recruitment information and online screening form. The website does not ask for any personal information. Participants can click a link from the web page to access a secure REDCap survey where they can provide their contact information (ie, name, email, and phone number) and complete an online screening form. Additionally, recruitment is completed via BuildClinical, a data-driven platform that helps academic researchers recruit participants for research studies more efficiently using social media, software, and machine learning. BuildClinical uses study-specific advertisements to engage participants on digital platforms such as Facebook (Meta Platforms, Inc), Google (Google LLC), WebMD (WebMD Health Corp), etc and redirect them to a study-specific landing page should they click it. On the landing page, the person can complete an online prescreen questionnaire that gets routed into BuildClinical’s platform. BuildClinical’s Secure Socket Layer encrypts all input information and keeps information private and HIPAA-compliant. Additional screening after the BuildClinical screen is then completed by the study staff, and eligible participants are emailed or texted an additional online screening form via a secure REDCap survey.

### Assignment of Interventions

Randomization is completed via the REDCap randomization module with an allocation sequence generated using a random number generator in Excel and with blocking on AUD symptoms and sex assigned at birth. The allocation sequence is uploaded into the randomization module of REDCap by unblinded study team members. A postdoctoral fellow generated the allocation sequence and uploaded it into the randomization module of REDCap, which then randomized participants to intervention conditions. Study staff who are blinded to the intervention condition enroll the participants.

Given the design of the study and use of behavioral interventions, only some members of the team could be blinded. Study participants are not blinded, given that they knew which continuing care program they were receiving. MBRP group facilitators and supervisors, as well as those delivering the orientation sessions, could also not be blinded. All outcome assessors, the study PI, and data analysts are blinded. The study PI is only unblinded on a case-by-case basis by an unblinded study team investigator in the case of a severe adverse event that involves participant allocation in the MBRP intervention condition and reporting to IRB and funding agencies regarding participation in the MBRP intervention.

### Data Collection and Management

Study data are collected and managed using REDCap [86,87], a secure, web-based software platform designed to support data capture for research studies hosted at the UNM CASAA. Data quality is promoted through careful programming to limit out-of-range responses. Study staff are continuously monitored to ensure data quality and protocol and regulatory adherence using applicable national and local regulations and standards.

Participants complete self-report questionnaire measures at baseline and every 6 months for 3 years following baseline. The measures were selected to assess specific constructs and were selected for previous evidence of producing reliable and valid scores, particularly in studies of AUD intervention programs. All measures and citations are provided in Table 3.

In addition to the self-report measures, we also collect physical mailing addresses in order to measure alcohol use via dried blood spot cards at baseline and the 3-year follow-up. A dried blood spot card or collection device is mailed to participants at baseline and month 36 to assess phosphatidylethanol (PEth), a biological marker that is sensitive to alcohol use and can be feasibly collected via mail [88,89]. The dried blood spot card collection kit, offered by the US Drug Testing Laboratories, requires a specimen amount that is 5 dried blood spots from a finger puncture or 5 mL of blood from a standard blood draw using an anticoagulation tube collection. Standard collection supplies provided include 2 lancets, 2 non–ethanol-based alcohol pads, gauze, a collection card, and the dried blood spot drying box. Returning the dried blood spot card is incentivized, and considerable effort is devoted to obtaining PEth samples from all participants. The dried blood spot cards are identified only via participant ID, shipped to the US Drug Testing Laboratories, who then email the study team with PEth values, which are recorded to the study REDCap database by trained research staff. No specimens are stored for future use, and no third parties have access to identifiable participant data.

MBRP facilitators are administered the MBRP self-report assessments listed in Table 3 above, including the Five Facet Mindfulness Questionnaire - Short Form, the Self-Compassion Scale - Short Form, the MBRP Practice Questionnaire, and the Applied Mindfulness Process Scale. MBRP facilitators also complete a measure of mindfulness meditation practice and retreat experience.

Process evaluation measures are guided by the RE-AIM (Reach, Effectiveness, Adoption, Implementation, Maintenance) model [90,91], which describes public health impact related to implementation research: (1) Reach: how many participants are impacted (eg, number of participants that engage in the MBRP program); (2) Effectiveness, such as rates of recovery and improvements in functioning among those who attend MBRP groups; (3) Adoption: continued engagement in offering the MBRP groups among the community clinician facilitators; (4) Implementation: extent to which the MBRP groups are attended and fidelity to the MBRP manual; and (5) Maintenance: the extent to which participants would continue attending MBRP groups and the extent to which community clinician facilitators would continue to offer the MBRP groups. We use a mixed methods framework. The quantitative metrics are gathered throughout the study. The qualitative interview guide is based on RE-AIM QUEST (Qualitative Evaluation for Systematic Translation) [90], tailored for MBRP. Qualitative interviews are conducted one-on-one with trained assessors via video calls. Facilitator participants and client participants are asked about their experiences with mindfulness generally, the THRIVE MBRP groups specifically, the THRIVE mobile app, and questions to assess potential facilitators and barriers to implementation of telehealth-delivered MBRP groups similar to those in THRIVE.

**Table 3. T3:** Constructs measured and specific assessments repeated every 6 months for 3 years.

Constructs	Assessment measures
Alcohol and drug use	Timeline Followback [67], alcohol and drug use past 6 months.
AUD^a^ severity	Alcohol Dependence Scale [92]
Diagnosis	*DSM-5^b^* AUD symptoms assessed by interview [93]
Alcohol problems	PROMIS^c^ alcohol consequences [75]
Craving	Penn Alcohol Craving Scale [79]
Psychosocial functioning	Psychosocial Functioning Inventory [94] WHOQOL-BREF^d^ [68] Purpose in Life [95]
Physical and mental health	PROMIS PROPr^e^ (functioning, sleep, pain, etc) [76], and PROMIS Meaning and Purpose measure [78]
Economic resources, housing, and food security	Employment status, income, transportation, housing, and food security
Social support	Social Support Questionnaire [96] Important People and Activities [97]
Incentive Salience items from AASE^f^ [98]	When I dream about taking a drink (AASE) When offered a drink in a social situation (AASE) When I feel physical need or craving for a drink (AASE) When I see others drinking (AASE)
Negative Emotionality items from AASE [98] and AUI^g^ [99]	When I am feeling depressed (AASE) When I am worried (AASE) When I feel angry inside (AASE) I start drinking to get over being depressed (AUI)
Executive Functioning items from the AASE [98], ADS^h^ [92], and OCDS^i^ [100]	Able to control amount you drink (ADS) Can usually stop after 1 or 2 drinks (ADS) Lose control over what you do when drinking (ADS) Success in stopping thoughts of drinking (OCDS) Effort to resist drinking (OCDS) Strong drive to consume alcohol (OCDS) Control over drinking (OCDS)
Treatment history, recovery resources, and recovery capital	Treatment and mutual-help history and goals from Recovery Resource Use Brief Assessment of Recovery Capital [101]
Self-efficacy	Substance Use Moderation Self-Efficacy Scale [102]
MBRP^j^ measures	Modified Group Cohesion Scale [103] Five Facet Mindfulness Questionnaire [104] Self-Compassion Scale [105] MBRP Practice Questionnaire Applied Mindfulness Process Scale [106]
Mutual-help measure	Multidimensional Measure of Mutual-Help Activity [107]

a AUD: alcohol use disorder.

b *DSM-5*: *Diagnostic and Statistical Manual for Mental Disorders *(Fifth Edition).

c PROMIS: Patient-Reported Outcomes Measurement Information System.

d WHOQOL-BREF: World Health Organization Quality of Life–Brief Version.

e PROPr: Patient-Reported Outcomes Measurement Information System Preference.

f AASE: Alcohol Abstinence Self-Efficacy Scale.

g AUI: Alcohol Use Inventory.

h ADS: Alcohol Dependence Scale.

i OCDS: Obsessive Compulsive Drinking Scale.

j MBRP: mindfulness-based relapse prevention.

### Retention

The investigative team is highly experienced in the conduct of clinical trials, and CASAA’s Program Evaluation Services staff routinely achieve follow-up rates at 1-year posttreatment of 85%‐90%, and they achieved 85% in the 3-year follow-up to Project MATCH [108]. These follow-up rates are achieved by creating a supportive atmosphere for research participants, through extensive participant tracking methods, and through compensation for assessments that is roughly equal to $25‐40/hour, by providing increasing compensation over time, and providing bonuses for completing at least 4 of the 6 follow-up assessment visits. Additional CASAA study staff send thank you cards, birthday cards, holiday cards, and study-branded materials (eg, pens, magnets, and study timeline) to participants to encourage retention. All outcome data are collected regardless of discontinuation or deviation from intervention protocols.

### Data Management

Data collection and accurate documentation are the responsibility of the study staff under the supervision of the study PI. Source documents and laboratory reports are reviewed by the study team and data entry staff, who will ensure that they are accurate and complete. The data are collected and maintained by experienced study staff who are trained in the use of clinical and research assessments using Good Clinical Practice tools. Study staff receive confidentiality and human participants’ protection training. All data are used for research purposes only and will not be revealed without the participants’ consent, and all entered data are checked first manually by another study staff member for correct entry and then statistically for correct form and range. Electronic data are stored in a database on a secure, password-protected server that is regularly backed up, and data collection forms are entered into REDCap. Data collection forms have been used in our previous studies and are retested prior to use. Data are monitored on a daily basis during the baseline period to track response rates and assess data quality. Protocol training is completed prior to enrollment. The research team is trained on best practices to follow the protocol procedures, consent, data collection, data entry, and query resolution. Scoring syntax that was developed for our prior studies is used to produce summary variables, and standard procedures are used for dealing with missing data.

### Statistical Methods

#### Primary Outcome Analysis

We use a generalized linear mixed model (GLMM) that can accommodate a binary outcome (recovery vs not recovery as defined by the NIAAA definition [17]) and random effects that correct for the nonindependence of repeated measures in longitudinal data to assess within-person change over time. The recovery binary variable is created using the 3 indicators included in the definition at each time point. AUD remission is based on not endorsing criteria for AUD (other than craving which may persist even during abstinence), cessation of heavy drinking is defined by no self-reported heavy drinking days, and improvements in functioning and well-being as measured by higher score (from baseline) on the WHOQOL-BREF [68] domain scores (each of 26 items scored from 1 to 5 on a response scale, which are then transformed linearly to a 0‐100 scale) and the 36-item Short Form Health Survey [69] Mental Health Component Score (scored on a 0‐100 scale). The analyses consist of estimating a GLMM with fixed effects of baseline sociodemographics and covariates used in randomization (sex and AUD severity), fixed effects of random assignment to MBRP versus online mutual support referral, and random effects of time.

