### Outcomes

#### Overview

All outcomes are assessed at each time point (baseline and at follow-up months: 6, 12, 18, 24, 30, and 36) and are studied over time with change from baseline to the last follow-up period as the analysis metric.

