#### Secondary Outcome Analyses

We use a GLMM that can accommodate binary secondary outcomes (achieving at least a 1-level reduction and achieving at least a 2-level reduction in WHO risk levels) and a general linear mixed model that can accommodate continuous secondary outcome measures. In all analyses, we include random effects that correct for the nonindependence of repeated measures in longitudinal data to assess within-person change in secondary outcomes over time. The analyses consist of estimating a mixed model with fixed effects of baseline sociodemographics and covariates used in randomization (sex and AUD severity), fixed effects of random assignment to MBRP versus online mutual support referral, and random effects of time.

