## Results

Funding for this study was awarded by the NIAAA (R01AA031159, PI: [name]) in August 2023. The version date for the latest protocol is December 22, 2025, and this is version 3.0 of the Protocol. Protocol changes included adding measures, adding an initial screening form online (vs via phone), increasing sample size, and adding procedures for participants to be recruited by other researchers. Recruitment began on September 13, 2023, and the last recruited participant was randomized on March 20, 2025. We randomized 470 individuals, of whom 432 completed orientation sessions, just going past the trial target of n=430 (100.5% recruited). The 6-month data collection has also been completed for all participants, and 369 completed the 6-month follow-up, 34 withdrew from the study prior to the 6-month follow-up; thus, the follow-up completion rate among those who continued in the study was 369/436 (86%) and the overall follow-up rate for all randomized participants was 369 out of 470 (78.5%).

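### The listed model terms leave out each secondary outcome's baseline value, which costs precision on the continuous outcomes and ignores who can succeed on the WHO risk-level outcomes

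*Protocol article*

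**What the plan says.** Under Statistical Methods, Primary Outcome Analysis, the Protocol article says what the recovery model consists of: "fixed effects of baseline sociodemographics and covariates used in randomization (sex and AUD severity"), plus randomized arm and random effects of time. Secondary Outcome Analyses gives the same list for the binary WHO risk-level outcomes and for all continuous outcomes: "estimating a mixed model with fixed effects of baseline sociodemographics and covariates used in randomization (sex and AUD severity").

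The Outcomes overview says that all outcomes are measured at baseline and at months 6 to 36, and that they "are studied over time with change from baseline to the last follow-up period as the analysis metric". The article does not say whether the baseline record enters the mixed models as a response row, is subtracted to form a change score, or is left out of the response.

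Three other places bear on the point:
- Reductions in WHO Risk Drinking Levels defines four levels from past-month drinking and counts drops of at least one or at least two levels.
- Textbox 1 admits people who already tried to cut down in the past 3 months, and asks for heavy drinking only at some time in the past 6 months.
- Assignment of Interventions bases the AUD severity factor on AUD symptoms.

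**The concern.** The baseline of the same measure is usually a stronger predictor of follow-up than sociodemographics are, and here it has already been collected. Leaving it out of a continuous-outcome model makes the standard error of the arm contrast larger than it needs to be. It also leaves chance baseline imbalance in the contrast. With 216 per arm the baseline difference has a standard error of √(2/216) = 0.096 SD. At a correlation of 0.5, an imbalance of 0.1 SD moves a change-score contrast by (1 − 0.5) × 0.1 = 0.05 SD, in a trial looking for a small effect.

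The WHO risk-level outcomes raise a different problem. Someone in the lowest level at baseline cannot drop one level, and someone in the lowest two cannot drop two. Given the entry criteria, such baselines are possible. Baseline level therefore fixes whether a participant can succeed at all, and the listed model does not contain it.

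**Working it through.** **The plan's own figure.** Sample Size Considerations states: "With a 2-tailed α of .05 and 430 participants (215 per group), we anticipate power greater than .90", for an effect taken from a prior trial, where "the difference at 12 months posttreatment on cessation of heavy drinking between MBRP and treatment as usual was a Cohen h=0.36". By the normal approximation, power = Φ(0.36 / √(2/215) − 1.96) = Φ(3.73 − 1.96) = 0.962. The statement reproduces. It does not depend on baseline adjustment.

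**Continuous secondary outcomes.** Inputs: 215 per arm (Sample Size Considerations) and unit SD at each visit. The documents give no baseline-to-follow-up correlation ρ, so 0.3, 0.5 and 0.6 are assumed. The contrast is at month 36.

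Relative variances are 1 for follow-up only, 2(1 − ρ) for change score, and 1 − ρ² for baseline-adjusted. The ratio of change score to adjusted is 2(1 − ρ)/(1 − ρ²) = 2/(1 + ρ). The follow-up-only standard error is √(2/215) = 0.0964; the others are this times the square root of the relative variance.

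| ρ | Adjusted variance vs follow-up only | Change-score variance vs follow-up only | Change score vs adjusted | SE follow-up only | SE change score | SE adjusted |
|---|---|---|---|---|---|---|
| 0.3 | 0.91 | 1.40 | 1.54 | 0.0964 | 0.1141 | 0.0920 |
| 0.5 | 0.75 | 1.00 | 1.33 | 0.0964 | 0.0964 | 0.0835 |
| 0.6 | 0.64 | 0.80 | 1.25 | 0.0964 | 0.0863 | 0.0772 |

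For an illustrative difference of 0.20 SD, follow-up-only power is 0.545. With adjustment it is 0.585 / 0.668 / 0.736.

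**If baseline is a response row.** This was computed for seven visits with compound symmetry at ρ = 0.3 and 0.5.
- With a baseline mean common to both arms, the month-36 standard error equals the adjusted one (0.0920 / 0.0835). Nothing is lost.
- With separate baseline means by arm, the change contrast has standard error 0.114 / 0.096, the same as change scores.
- With only an arm main effect, which is the only arm term listed, the null baseline difference is averaged in. A constant follow-up effect then shrinks to 6/7 of its size.

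**WHO risk-level outcomes.** With four ordered levels, a one-level drop is impossible from the lowest level, and a two-level drop is impossible from the lowest two. The article does not give the baseline distribution, so the number affected cannot be computed.

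**Recovery.** The third component requires scores above the participant's own baseline, so recovery at baseline is 0 for everyone and cannot serve as a covariate. Baseline component scores do vary and may be prognostic. Assume a mean gain of 0.3 SD. The chance of any rise is then Φ((0.3 − (1 − ρ)b)/√(1 − ρ²)) for someone b SD above the baseline mean. At ρ = 0.5 this is Φ(−0.2/0.866) = 0.41 at b = 1 and Φ(0.8/0.866) = 0.82 at b = −1.

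In a logistic model, however, adding a prognostic covariate does not narrow the standard error of the log odds ratio. In an illustrative simulation of ordinary logistic regression with 432 participants, a covariate with log odds ratio 1.0 per SD moved that standard error from 0.202 to 0.224 and power from 0.87 to 0.91. With 0.5 per SD the moves were 0.205 to 0.211 and 0.93 to 0.94. The gain is in power, and it is modest.

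**The case against.** The strongest reply is that no loss is shown. The secondary models concern within-person change over repeated measures, baseline is one of the assessed times, and a mixed model with baseline in the response can recover all of its information. The article is also condensed: it names no fixed time effect, and a fuller plan may settle how baseline enters. This stands in part, because one specification does lose nothing. But that specification needs a baseline mean held equal across arms. The article does not state this, and a single arm main effect does not deliver it. The text also gives a definite term list rather than leaving the model open.

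Three further replies hold and set the limits of the point:
- AUD severity is already in every model, so the AUD symptom outcome largely has its baseline adjustment.
- Under randomization the omission does not bias the comparison, and ordinary standard errors already allow for chance imbalance.
- The variance factors rest on assumed correlations and apply to continuous outcomes.

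A reader might infer that precision is lost on every endpoint, including the primary, and that adjustment is worth 432 / 0.75 = 576 participants. The documents do not support that. Recovery has no informative baseline value, a logistic model does not gain a smaller standard error from adjustment, and 576 applies only to a continuous outcome at ρ = 0.5, not to recovery or the WHO risk-level outcomes.

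**Conclusion.** The point holds for the secondary outcomes. For continuous measures other than AUD symptoms, analysing follow-up values without baseline forgoes a variance reduction of 9% / 25% / 36% at assumed correlations of 0.3 / 0.5 / 0.6. Analysing change without baseline adjustment gives 1.54 / 1.33 / 1.25 times the variance available. These figures assume equal SD at each visit, and the response-row comparison also assumes compound symmetry. The loss vanishes only under a common-baseline-mean model that the article does not state.

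For the WHO one- and two-level reductions, the omission of baseline level is plain from the definition of the outcome. Its numerical effect depends on a baseline distribution that is not given.

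For recovery nothing is missing in the own-baseline sense, and adjustment for component scores is an option. The comparison remains valid under randomization, and the stated power above .90 is unaffected.

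**What to change.** In Secondary Outcome Analyses:
- For each continuous outcome, model the six follow-up values with that measure's own baseline as a covariate and arm-by-visit terms. Equivalently, keep baseline in the response with its mean constrained equal across arms. State which is used.
- Add baseline WHO risk level to both risk-level models. Participants at a level from which success is impossible have no events by definition, so also state how that stratum is handled in fitting.

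In Primary Outcome Analysis, optionally prespecify baseline percent heavy drinking days and the baseline WHOQOL-BREF and SF-36 mental health scores as prognostic covariates. Justify this by a modest power gain, not by a smaller standard error.

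The cost is wording and a longer covariate list, since the protocol has these measured at baseline. Odds ratios from the binary models become conditional on the added covariates and should be described as such. Follow-up is still under way and the analysts are blinded, so the change can still be prespecified.
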